### Statistical analyses

For every wave of data collection, the main analysis will treat the outcomes as continuous variables. This will enable us to understand the impact of TDM in any change observed in physical activity, mental health and educational attainment for each child through each successive year of primary school.

We will use a linear multilevel mixed effect regression model to estimate the mean difference in MVPA values between TDM schools and non-TDM schools across follow-up and at each follow-up wave. Children will be included as a random intercept with fixed effects for wave, intervention group, wave-by-intervention group interaction and baseline (Wave 1) MVPA. School will also be included in the model as a random effect and adjustments for covariates including participation in TDM and sociodemographic variables will be included. Baseline adjusted group differences will be reported with a 95% CI for each wave. An additional model without wave-by-intervention interaction will be fitted to provide an estimate of the overall intervention effect across follow-up.

Based on previous studies,^40 43^ we expect data from children to vary throughout each wave of data collection as compliance in the youngest age groups (5–6 years) may differ compared with when they are measured later (aged 10–11 years). Decisions on valid accelerometer data to include in the analysis will be made when reviewing the data and based on previous literature.

Linear multilevel mixed effect regression models as described for MVPA will be repeated for the outcomes of mental health and educational attainment.

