**Methods and analysis:**

iMprOVE is a longitudinal quasi-experimental cohort study. We will send a survey to all state-funded primary schools in Greater London to identify participation in TDM. The survey responses will be used for non-random allocation to either the intervention group (Daily Mile schools) or to the control group (non-Daily Mile schools). We aim to recruit 3533 year 1 children (aged 5–6 years) from 77 primary schools and follow them up annually until the end of their primary school years. Data collection taking place at baseline (children in school year 1) and each primary school year thereafter includes device-based measures of moderate-to-vigorous physical activity (MVPA) and questionnaires to measure mental health (Strengths and Difficulties Questionnaire) and educational attainment (ratings from ‘below expected’ to ‘above expected levels’). The primary outcome is the mean change in MVPA minutes from baseline to year 6 during the school day among the intervention group compared with controls. We will use multilevel linear regression models adjusting for sociodemographic data and participation in TDM. The study is powered to detect a 10% (5.5 min) difference between the intervention and control group which would be considered clinically significant.

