## Methods and analysis

### Study design

The iMprOVE Study is a longitudinal quasi-experimental cohort study of state-funded primary schools located in Greater London which has a diverse multi-ethnic urban population. The target population is children in schools that participate in TDM (intervention group) compared with those that do not participate in TDM or any other active mile initiative (control group). We will assess children in the first year of primary school (aged 5–6 years) and follow them up annually in each successive primary school year until the end of primary school (year 6, children aged 10–11 years). In total, we will collect six waves of data (figure 1).

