### Data collection time points

There will be one data collection in each school year. Data collection for baseline (Wave 1) will begin from January 2021 (allowing for regular TDM activity to take place if implemented by the school) and will continue until we have met our sample size targets. Control group participants will be assessed simultaneously to the intervention group (figure 1).

For consistency and potential seasonal variation in activity levels, we aim to carry out follow-up assessments during the same month as baseline assessments in each year until the end of data collection in 2026 (figure 1).

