### Sample size

Our sample size is based on the primary outcome of mean MVPA (minutes) per day allowing for the clustering of children in the same school and the primary analysis adjusting for baseline minutes of MVPA. Based on our previous work, there is an average of 46 children per state-funded primary school in Greater London.^11^

We conducted a sample size calculation (using STATA V.15.1) that produced a total sample of 3533 children (approximately 1767 children in the intervention and control groups) across 77 schools to give the study 90% power to detect a 5.5 min increase in the mean daily average MVPA minutes between children in TDM schools compared with non-TDM schools, assuming a mean daily average MVPA of 53 min (SD 22) in the control group based on the study by Chesham *et al*.^15^ This has been inflated to allow for 60% attrition across the follow-up period and assumes a two-sided alpha equal to 0.05. To allow for the analyses to include clustering at school level, we have applied an intraclass correlation coefficient of 0.05 to our calculation (online supplemental table 3). An increase of just over 5 min of MVPA per day equal to a 10% difference would be clinically significant to increase physical activity among the proportion of children who participate in less than an average of 30 min per day.

10.1136/bmjopen-2020-045879.supp3Supplementary data

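### The MVPA model adjusts every follow-up wave with one baseline slope; if that slope changes over follow-up, any baseline gap between the groups shifts the Year 6 difference

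*Protocol article*

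**What the plan says.** The protocol article gives the MVPA model explicitly under Statistical analyses: "Children will be included as a random intercept with fixed effects for wave, intervention group, wave-by-intervention group interaction and baseline (Wave 1) MVPA", plus a school random effect and covariates. Only group is interacted with wave. The section then says what is reported: "Baseline adjusted group differences will be reported with a 95% CI for each wave". The same model is to be repeated for mental health and educational attainment.

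The Abstract ties the primary outcome, a comparison against the control group, to the last wave: "The primary outcome is the mean change in MVPA minutes from baseline to year 6 during the school day among the intervention group compared with". Study design adds "In total, we will collect six waves of data", which means one baseline and five follow-ups.

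Three further statements bear on whether the groups start level:
- The Abstract describes allocation as non-random, from survey replies. Under School survey and recruitment, the intervention group consists of schools that already report delivering TDM.
- Data collection time points starts Wave 1 from January 2021, "allowing for regular TDM activity to take place if implemented by the school".
- The Discussion expects some selection bias.

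The article gives no baseline-to-follow-up slope or correlation at any wave.

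**The concern.** With a single baseline term, one coefficient serves all five follow-up waves. MVPA at age 5–6 may well predict MVPA a year later better than MVPA five years later. If so, the fitted coefficient is a compromise: too small for Wave 2 and too large for Year 6.

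In a randomised trial the expected baseline difference is zero, so this would mainly cost a little precision. Here a baseline gap is foreseeable, and the slope error multiplies that gap without averaging out. At stake are the Year 6 contrast and the wave-by-group pattern. Part of an apparent fading or growth of the TDM effect could come from the slope restriction.

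**Working it through.** **Inputs from the article.** Five follow-up waves (Study design). From Sample size: target "to detect a 5.5 min increase in the mean daily average MVPA minutes", SD 22, 90% power, two-sided alpha 0.05, 60% attrition, ICC 0.05, 46 children per school.

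**Can a slope be recovered from the sample size?** No.
- Per arm: 2 × (1.960 + 1.282)² × 22² / 5.5² = 336.24.
- With 46 per school the design effect is 1 + 45 × 0.05 = 3.25. The total is 2 × 336.24 × 3.25 / 0.4 = 5464, not 3533.
- A baseline correlation of 0.6 multiplies this by 1 − 0.36 = 0.64 and gives 3497.
- With 23 per school (design effect 2.10) and no correlation, the total is 2 × 336.24 × 2.10 / 0.4 = 3530.

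Two different input sets come close to 3533, so the total does not identify a correlation. Supplemental table 3 is not shown. The slopes below are therefore assumptions.

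**Formula.** At wave w the adjusted difference is (raw difference at w) − slope × (baseline gap). If the model uses a common slope b where the wave's own slope is b_w, the adjustment is off by (b − b_w) × gap.

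**Common slope.** This is approximated as a weighted mean of the wave slopes, with either equal weights or retention weights of 0.88, 0.76, 0.64, 0.52, 0.40. Of these, only the final 0.40 follows from the article. Example for set B: (0.528 + 0.380 + 0.288 + 0.208 + 0.120) / 3.20 = 0.476.

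| Assumed slopes, Waves 2–6 | Weights | Common slope | Excess at Year 6 | Shortfall at Wave 2 | Year 6 shift, 2 min gap | Year 6 shift, 5.5 min gap |
|---|---|---|---|---|---|---|
| A: 0.60, 0.55, 0.50, 0.45, 0.40 | equal | 0.500 | 0.100 | 0.100 | 0.20 | 0.55 |
| A | retention | 0.519 | 0.119 | 0.081 | 0.24 | 0.65 |
| B: 0.60, 0.50, 0.45, 0.40, 0.30 | equal | 0.450 | 0.150 | 0.150 | 0.30 | 0.83 |
| B | retention | 0.476 | 0.176 | 0.124 | 0.35 | 0.97 |
| constant 0.50 | either | 0.500 | 0 | 0 | 0 | 0 |

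Shifts are in minutes. At a 5.5 min gap they are 10% to 18% of the target. With equal weights the misfit at Year 6 and at Wave 2 is the same size; Year 6 is worse only under the retention weights.

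**Check by simulation.** One large data set per setting (14,132 children) was fitted with a child random intercept, wave, group and wave-by-group. Baseline was entered once as a single term and once by wave. Assumed values were baseline SD 22, child SD 10, residual SD 14, a 5.5 min baseline gap and a true effect of 5.5 min. The school effect was left out. Year 6 estimates with 60% attrition:

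| Slope path | Single term | By wave | Shift |
|---|---|---|---|
| constant 0.50 | 5.06 | 5.04 | 0.02 |
| 0.60 to 0.40 | 4.43 | 5.04 | −0.61 |
| 0.60 to 0.30 | 4.11 | 5.04 | −0.92 |
| 0.70 to 0.20 (stress case) | 3.49 | 5.04 | −1.55 |

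Shifts are taken from unrounded estimates. Without attrition they are 0.00, −0.55, −0.82 and −1.37. With dropout the formula is slightly high: putting in the fitted common slopes gives (0.530 − 0.40) × 5.5 = 0.72 and (0.493 − 0.30) × 5.5 = 1.06, against 0.61 and 0.92 observed.

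**Against the design's precision.** 90% power for 5.5 min implies a standard error of about 5.5 / 3.24 = 1.7 min. Shifts of 0.20 to 0.97 min are 0.1 to 0.6 standard errors.

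**The case against.** The other side has five fair points.

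1. **The error needs two conditions.** A reader might infer that unequal baselines alone make the Year 6 adjustment wrong. The article does not support that: the slope must also change over follow-up, and nothing in it says that it does. This stands and limits the claim.
2. **The size is assumed and modest.** A 5.5 min gap equals the whole target effect; at 2 min the shift is 4% to 6% of target. This stands. The 60% attrition in the article does, however, pull the common slope toward the early waves.
3. **Year 6 need not be the worst wave.** That is correct under equal weights. The planned sensitivity analysis with imputed MVPA would move toward equal weights, and so toward the smaller shifts.
4. **The right amount of adjustment is itself open.** The Abstract describes change from baseline, and a contrast of changes subtracts the whole gap (slope 1). Change-score and baseline-adjusted contrasts answer different questions when groups start unequal. That is a separate matter. Once the plan has chosen baseline adjustment, it gives no reason to force one slope on all waves.
5. **The specification is conventional, and an analysis plan not shown could add the term.** That is true. But the article lists the fixed effects and interacts one of them with wave, so the restriction belongs to the model as stated.

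**Conclusion.** The point holds conditionally. As listed, the model has no baseline-by-wave term. If the baseline slope changes between ages 5–6 and 10–11, the Year 6 difference is mis-adjusted in proportion to the baseline gap. Under assumed slopes falling from 0.6 to 0.3–0.4, the shift is about 0.1 to 0.18 min per minute of gap. It vanishes if either condition fails.

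The direction is not fixed. With a falling slope, the TDM difference at Year 6 is understated if TDM schools start higher and overstated if control schools start higher.

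Two stronger readings should be resisted. The article does not show that the Year 6 estimate will be biased, because it quantifies neither the slope change nor the gap. Nor would freeing the slope make the baseline adjustment right. Wave 1 MVPA is measured with TDM already running, so adjusting for it may remove part of the effect. At Year 6 slopes of 0.3 to 0.4 and a 5.5 min gap, 0.3 × 5.5 = 1.65 to 0.4 × 5.5 = 2.2 min would still be subtracted, more than the interaction corrects.

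**What to change.** Add a baseline MVPA-by-wave interaction to the MVPA model and take the Year 6 difference from that model. Do the same in the mental health and educational attainment models, each with its own baseline value.

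The cost is four extra parameters per model. No new data are needed and the sample size does not change. In the simulation the two models agreed within 0.02 min when the slope was constant, so little is lost where the term is not needed.

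Add a sentence saying that the interaction frees the slope but does not resolve the exposure of intervention schools to TDM at Wave 1, so baseline-adjusted differences may still omit part of the effect.

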#### Subgroup analysis

To address inequalities, we will examine MVPA of children in TDM and non-TDM schools according to area level deprivation (a measure of poverty) using the Index of Multiple Deprivation.^44^

#### Sensitivity analyses

We anticipate that during the study period, schools that are assigned to intervention group may stop TDM and schools assigned to the control group may take up TDM. We will conduct a series of sensitivity analyses to explore TDM impacts in children who engage in TDM in some year groups only. We will also consider seasonal effects on implementation of TDM and MVPA overall dependent on the month children are assessed. In addition, missing data for MVPA in the follow-up waves will be imputed and included separately to a complete case analysis.

All analyses will be carried out using STATA V.15 (StataCorp, Texas, USA).

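### Imputation is limited to follow-up waves while Wave 1 MVPA is a model covariate, so children without a valid Wave 1 recording drop out of both the primary MVPA model and its missing-data sensitivity analysis

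*Protocol article*

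**What the plan says.** The Statistical analyses section of the protocol article specifies a linear mixed model for MVPA with random effects for child and school and with "fixed effects for wave, intervention group, wave-by-intervention group interaction and baseline (Wave 1) MVPA". Group differences are estimated "across follow-up and at each follow-up wave" and reported as baseline-adjusted. The one additional model drops the wave-by-group interaction and changes nothing else.

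The Sensitivity analyses section then states that "missing data for MVPA in the follow-up waves will be imputed and included separately to a complete case analysis". The other sensitivity analyses there concern schools that start or stop The Daily Mile (TDM) and the month of measurement. The article describes no imputation of Wave 1 MVPA and no other method for a missing baseline.

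Two further statements bear on how often Wave 1 may be missing. The article expects that "compliance in the youngest age groups (5–6 years) may differ compared with when they are measured later (aged 10–11 years"), and ages 5–6 are the Wave 1 ages. It also leaves the validity rule open: "Decisions on valid accelerometer data to include in the analysis will be made when reviewing the data".

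**The concern.** A mixed model copes with missing outcome values, but a row with a missing covariate cannot enter the fit. Wave 1 MVPA is a single value per child, so one invalid recording at age 5–6 removes all of that child's follow-up rows, up to five. Imputing follow-up MVPA does not help, because those imputed outcomes still have no baseline value beside them.

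The children concerned stay in the study and are measured every year. They are left out of the primary MVPA model because of their wear at the age for which the article itself expects compliance to differ. The analysis meant to test robustness to missing data leaves out the same children, so agreement between it and the complete case analysis would say nothing about this exclusion.

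**Working it through.** **The plan's own figure.** Inputs from the Sample size section: difference 5.5 min, SD 22, two-sided alpha 0.05, power 90%, ICC 0.05, 46 children per school, 60% attrition.

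- Per group without clustering: 2 × [22 × (1.960 + 1.282) / 5.5]² = 336.2, so 337.
- Design effect: 1 + (46 − 1) × 0.05 = 3.25.
- Schools per group: 337 × 3.25 / 46 = 23.8, so 24. In total 48 schools and 48 × 46 = 2208 children.
- Inflation: 2208 × 1.6 = 3532.8 and 48 × 1.6 = 76.8.

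This matches the stated 3533 children and 77 schools. The only loss allowed for is attrition across follow-up. Nothing is added for missing baselines. (The match comes from multiplying by 1.6. Taken literally, 60% attrition leaves 3533 × 0.4 = 1413 children, which is the base used below. That is a separate matter.)

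**The exclusion itself.** In a simulated data set of 77 schools with 46 children each and 20% of baselines missing at random, 3541 children had at least one follow-up value. Only 2860 could enter a model with the baseline as covariate (11423 of 14131 rows). All follow-up rows of the other 3541 − 2860 = 681 children were lost.

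**Size of the precision loss.** The article gives no rate p of invalid Wave 1 data, so p is an assumption. Further assumptions: p is independent of later dropout, all 77 schools stay, the groups are equal in size, and no precision is gained from baseline adjustment.

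- Year 6 children: N = 3533 × 0.4 × (1 − p)
- Children per school: m = N / 77
- Design effect: DE = 1 + (m − 1) × 0.05
- Standard error: SE = 22 × √(4 × DE / N)

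| p | Excluded (3533 × p) | N at Year 6 | m | DE | SE (min) | SE ratio | Power for 5.5 min |
|---|---|---|---|---|---|---|---|
| 0 | 0 | 1413 | 18.35 | 1.868 | 1.60 | 1 | 93.0% |
| 10% | 353 | 1272 | 16.52 | 1.776 | 1.64 | 1.03 | 91.7% |
| 20% | 707 | 1131 | 14.68 | 1.684 | 1.70 | 1.06 | 90.0% |
| 30% | 1060 | 989 | 12.85 | 1.592 | 1.77 | 1.10 | 87.6% |

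**When the exclusion can bias the result.** In a correctly specified model, the adjusted group difference is conditional on group, baseline MVPA and covariates. Dropping records for reasons that depend only on those variables leaves it unbiased. A simulation with 78 schools of 46 children, ICC about 0.05, a true difference of 5.5 min and 23% to 32% of baselines missing shows this (Monte Carlo SE about 0.05):

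- missing by baseline activity: 5.50
- missing by group: 5.41
- missing by both, with interaction: 5.55
- missing also by later MVPA given baseline and group: 7.16

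Only the last departs clearly from 5.5. Its size and direction belong to the mechanism chosen for that run and are not a forecast for this study. Dependence on later MVPA is a necessary condition for bias, not a sufficient one.

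**The case against.** The strongest reply is that this is a condensed article and that handling of a missing baseline covariate belongs in an analysis plan. Nowhere does the article say that such children are excluded. That is inferred from how a regression treats a missing covariate, and an unseen analysis plan could widen the imputation. This limits the point to the analyses as described. It does not remove it, because the article is not silent: it states the scope of imputation, and that scope omits Wave 1.

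Second, the Abstract says that "The primary outcome is the mean change in MVPA minutes from baseline to year 6 during the school day". A child without Wave 1 has no observed change, and restricting the analysis to children with a baseline is common. That is a defensible primary choice. It does not justify a sensitivity analysis for missing data that carries the same restriction.

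Third, the Data collection time points section says that baseline collection continues until the sample size targets are reached. If those targets count children with usable Wave 1 recordings, there is no shortfall in precision against the plan. This stands. The article does not say how the targets are counted.

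A reader might infer that the group difference is biased as soon as children with poor wear differ in activity, or wear differs between TDM and control schools. The documents do not support that. Neither condition is enough on its own, as shown in the working.

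A reader might also infer that these children are lost to the whole study. That goes too far as well. Nothing stated ties the segmented MVPA analyses under Outcomes and measures to a Wave 1 value. The mental health and attainment models need not lose these children either, if the baseline there is that of the outcome concerned.

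**Conclusion.** The point holds for the primary MVPA model and its imputed sensitivity analysis as the article describes them: children without a valid Wave 1 recording contribute to neither. The loss of precision is modest. At an assumed 10% to 30% invalid Wave 1 data, it amounts to 353 to 1060 children, a standard error about 3% to 10% larger, and power of 91.7% to 87.6% against 93.0% with no such loss. It could be nil if recruitment counts only children with usable baselines.

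Bias is possible but not shown. It requires Wave 1 missingness to be related to later MVPA given baseline, group and covariates, and the documents offer no means of judging whether it is. Allocation is not randomised, so balance between the groups in this respect cannot be taken for granted. The main weakness is that the planned check cannot detect such bias. Correcting this is worthwhile because it is cheap, not because the result is known to be wrong.

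**What to change.** In the Sensitivity analyses section, extend the imputation to MVPA missing at any wave, including Wave 1. Use a multilevel imputation model (child within school) that includes group, MVPA at the other waves, C-PAQ, the covariates and month of measurement. Keep the baseline-adjusted model of the Statistical analyses section as the analysis model. In the imputed analysis, include every enrolled child with at least one valid follow-up recording. Report the number and proportion of children without valid Wave 1 MVPA by group.

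Fitting Wave 1 MVPA as one of the repeated outcomes would also keep these children, but it should not be presented as equivalent. Without equal baseline means imposed, it estimates a difference in change rather than the baseline-adjusted difference. Imposing equal baselines is not justified when schools are allocated by existing participation.

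The cost is a change of wording and a little more analysis work, with no new data. The imputed analysis relies on data being missing at random. If Wave 1 missingness depends on the unseen baseline value itself, that assumption fails while the complete case estimate may still be sound. The two should therefore be reported side by side, as the article already intends.
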